# Effectiveness and cost-effectiveness of an electronic mindfulness-based intervention to improve maternal mental health in the peripartum: study protocol for a randomised controlled trial

**DOI:** 10.1186/s13063-023-07746-7

**Published:** 2023-11-23

**Keywords:** Mindfulness, Maternal mental health, Maternity, Peripartum, Intervention

## Abstract

**Background:**

Perinatal women are highly vulnerable to developing mental health issues and particularly susceptible to a recurrence of psychiatric illness. Poor mental health during the perinatal period can have long-term impacts on the physical and psychiatric health of both mother and child. A potentially useful strategy to improve women’s mental health is through a mobile application teaching mindfulness, an evidence-based technique helping individuals focus on the present moment.

**Methods:**

A mixed method, prospective randomised controlled trial. The study group comprise women aged 18 years and over, who are attending the public and private maternity clinics at Mater Mothers’ Hospital. A sample of 360 prenatal women will be randomised into the intervention group (with the use of the mindfulness app) or usual care. Participants will remain in the study for 11 months and will be assessed at four timepoints for changes in postnatal depression, mother-infant bonding, and quality of life. A cost-effectiveness evaluation will also be conducted using quality-adjusted life year (QALY) calculations. A random selection of intervention participants will be invited to attend focus groups to give feedback on the mindfulness app.

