### Sample size {14}

The necessary sample size was calculated using the public access software G*Power 3.1.9.7 for Windows [20]. The primary outcome of depression, as measured by the EPDS, was used to estimate the required sample size. Previous meta-analyses that found mindfulness in the perinatal period reduced depression scores with an effect size of *d* = 0.59 [21, 22]. The sample size calculation was therefore based on the estimation of a medium intervention effect (*d* = 0.50). A sample size of 128 was required to compare differences at timepoint 4, with 80% statistical power, a two-tailed significance level of 5%, and a 1:1 allocation ratio. Previous studies have reported high attrition rates of 20–45% [23, 24]. Accounting for an attrition rate of 40%, a final sample size of 214, with 107 individuals in each group, will be required.

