### Recruitment {15}

The study will recruit women for up to 3 months, or until the sample size is achieved. The study site manages the treatment of over 800 women per month. Given the sample requirement is less than half this amount, we anticipate achieving full recruitment within 2 months.

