### Interim analyses {21b}

No interim analyses are planned. Data collection will cease once the sample size has been achieved.

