## Trial status

Protocol version 3.1 (5 September 2022) was approved by the Mater Ethics Committee on 17 October 2022 (Ref: AM/MML/83589 (V3)). Recruitment for the trial will begin in November 2023 and will be completed by July 2024.

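### The abstract says 360 women will be randomised, the sample size section derives 214, and the recruitment stop does not say which total applies

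*Protocol article*

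**What the plan says.** All places are in the protocol article.

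- Abstract, Methods: "A sample of 360 prenatal women will be randomised into the intervention group". The sentence goes on to name usual care as the other arm, so 360 is the total over both arms.
- Sample size {14}: "A sample size of 128 was required to compare differences at timepoint 4", for d = 0.50, 80% power, a two-sided 5% level and equal allocation. It cites attrition of 20% to 45% from other studies, and its conclusion reads "Accounting for an attrition rate of 40%, a final sample size of 214, with 107 individuals in each group, will be required". This total, too, covers both arms.
- On when enrolment ends, the section Recruitment {15} has this rule: "The study will recruit women for up to 3 months, or until the sample size is achieved". It compares the requirement with a flow of over 800 women a month: "Given the sample requirement is less than half this amount, we anticipate achieving full recruitment within 2 months".
- Interim analyses {21b}: "Data collection will cease once the sample size has been achieved".

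No other place in the article repeats, derives or explains 360.

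**The concern.** The number to be randomised is a basic design figure, and the article gives two values for it. They cannot be reconciled by reading one as randomised and the other as evaluable, because Sample size {14} gives the evaluable number separately (128) and 214 already contains the attrition allowance.

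The sentence that ends recruitment refers to the sample size without a number, so it does not settle the matter. If 360 is the real target, the sample size section does not justify the trial's size and its 80% power is not the power of the trial. If 214 is the target, the Abstract misstates the trial.

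**Working it through.** **Inputs**, all from Sample size {14} except the last: d = 0.50; two-sided alpha 0.05; power 0.80; allocation 1:1; assumed attrition 40%; cited attrition 20% to 45%; total of 360 from the Abstract.

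**1. Reproducing the plan's own figure.** The normal approximation for two means is n per arm = 2(z₀.₉₇₅ + z₀.₈₀)² / d² = 2(1.960 + 0.842)² / 0.25 = 62.8, so 63. The noncentral t calculation gives 63.77, so 64 per arm and 128 in total, as stated. Inflating for attrition: 128 / (1 − 0.40) = 213.3, rounded up to 214, or 107 per arm. This also agrees.

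**2. Does 360 follow from the same inputs?**

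- 20% attrition: 128 / 0.80 = 160.
- 40% attrition: 128 / 0.60 = 213.3, so 214.
- 45% attrition: 128 / 0.55 = 232.7, so 233.

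For 360 randomised women to leave 128, attrition would have to be 1 − 128/360 = 64%, well outside the cited range. Raising power to 90% at the worst cited attrition still gives only 313. Inflating 214 a second time gives 214 / 0.60 = 357, close to 360, but nothing in the article says this was done; it is conjecture about the origin.

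**3. What each total implies** (two-sample t-test, two-sided 5%; completers = total × (1 − attrition)):

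| Randomised | Attrition | Completers | Power for d = 0.50 | d detectable at 80% power |
|---|---|---|---|---|
| 214 | 20% | 171 | 90.2% | 0.43 |
| 214 | 40% | 128 | 80.3% | 0.50 |
| 214 | 45% | 118 | 76.7% | 0.52 |
| 360 | 20% | 288 | 98.8% | 0.33 |
| 360 | 40% | 216 | 95.5% | 0.38 |
| 360 | 45% | 198 | 93.8% | 0.40 |

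The totals differ by 360 − 214 = 146 women, and 146 / 214 = 68%.

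**4. Does the recruitment text choose between them?** 214 / 800 = 27% and 360 / 800 = 45%. Both are less than half of the monthly flow, so the sentence is true under either total.

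**The case against.** The best case on the other side is that the full derivation sits in the body, is correct, and gives one number, while 360 appears once, in an abstract. No calculation fails, no test or type I error changes, and at the planned 40% attrition neither total underpowers the trial for d = 0.50. All of that stands. It limits the consequences but does not remove the contradiction, and nothing in the article marks 360 as a slip.

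Several stronger readings are tempting, and the article does not support them:

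- **That power and the detectable effect are undefined.** Sample size {14} fixes 80% power, the two-sided 5% level and d = 0.50 for 214, and these reproduce. What is open is which total applies.
- **That the remark about less than half the monthly flow shows 360 to be the real target.** It is true of both totals and needs no correction under either.
- **That two totals leave room for a stop guided by results.** The primary outcome is EPDS at 6 months postpartum, about 11 months after entry. Recruitment lasts at most 3 months by Recruitment {15}, or about nine months on the longest reading of Trial status. Primary outcome data should therefore accrue after recruitment has closed; at most, surveys from earlier timepoints would exist. No interim analysis is planned and the analyst is blinded.
- **That the sentence in Interim analyses {21b} would end follow-up early.** Trial design {8} and Outcomes {12} fix four assessments up to 6 months postpartum. The sentence is loosely worded and worth correcting, but it does not threaten the endpoint.
- **That the recruitment period is contradictory.** Trial status says "Recruitment for the trial will begin in November 2023 and will be completed by July 2024". That gives a latest completion date, and a window of up to 3 months from November 2023 satisfies it. The two statements are loosely aligned, not in strict conflict.

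**Conclusion.** The contradiction is real. The article gives two incompatible totals, 360 and 214, which differ by 146 women. Only 214 is derived, and its derivation is correct. The inputs stated for 214 give 160 to 233 over the cited attrition range, so they do not support 360.

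The practical effect is on which power describes the trial: about 80% for d = 0.50 with 214, or about 95.5% with 360. Both figures assume 40% attrition, a two-sample t-test at the two-sided 5% level and equal arms. The defect is one of specification and reporting. It does not show the trial to be underpowered or its analysis to be invalid, and 360, if intended, would give more power than stated, with 146 additional women for whom no justification is given.

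**What to change.** State one total everywhere.

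- **If 214 is the target**, as the article's own calculation indicates, correct the Abstract.
- **If 360 is the target**, add to Sample size {14} the assumptions that produced it, and restate the power: about 95% for d = 0.50 at 40% attrition. Choosing d = 0.38 because 360 happens to detect it with 80% power would be working backwards; the article's effect-size rationale is a meta-analytic 0.59 reduced to 0.50.
- **In Recruitment {15}**, put the chosen number into the stopping sentence.
- **In Interim analyses {21b}**, say that recruitment ceases when that number has been randomised and that follow-up continues to 6 months postpartum for every participant.

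If 214 is kept, the cost is a correction to the Abstract and two sentences in the body, with no additional participants. If 360 is kept, the cost is a proper justification for 146 more women than the present calculation requires. The registry entry was not available for this review, so its figure should be checked against the chosen total.

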**Discussion:**

Previous studies have found mindfulness interventions can reduce stress, anxiety, depression, and sleep disturbances in a prenatal population. The risks of the intervention are low, but could be of significant benefit for women who are unable to attend face-to-face appointments due to geographical, financial, or time barriers; during endemic or pandemic scenarios; or due to health or mobility issues.

**Trial registration:**

This study was approved by the Mater Misericordiae Human Research Ethics Committee (83,589). Australian New Zealand Clinical Trials Registry (ANZCTR) ACTRN12622001581752 (https://www.anzctr.org.au/Trial/Registration/TrialReview.aspx?id=385107&isReview=true). Registered on 22 Dec. 2022.

**Supplementary Information:**

The online version contains supplementary material available at 10.1186/s13063-023-07746-7.

## Administrative information

Note: the numbers in curly brackets in this protocol refer to SPIRIT checklist item numbers. The order of the items has been modified to group similar items (see http://www.equator-network.org/reporting-guidelines/spirit-2013-statement-defining-standard-protocol-items-for-clinical-trials/).

## Introduction

### Background and rationale {6a}

The perinatal period is associated with a significantly increased risk of onset and relapse of mental health conditions, with self-harm being the most common cause of perinatal mortality [1, 2]. Pre- and post-natal psychiatric illness is a significant global health issue, affecting around 20% of women while remaining largely underdiagnosed and undertreated [2–5]. An estimated one in five women will experience postnatal depression or anxiety in the first year after the birth of their child [2, 6, 7]. Approximately one in 10 women will experience clinically significant symptoms of depression during pregnancy [6].

If untreated, perinatal health issues, such as depression and anxiety, can result in long-term emotional, social, and wellbeing impacts for parents, children, and families. Poor maternal mental health can lead to suboptimal infant outcomes in the future (e.g. low birth-weight infants, suboptimal development, later-life mental illness) and less favourable mother-baby bonding [8–10]. Maternal anxiety and depression during pregnancy are associated with an increased likelihood of difficult infant temperament and behavioural problems in infancy [11]. Maternal mental illness in the postpartum period has been found to impact attachment and contribute to developmental delays in motor function, language acquisition, cognitive skills, emotional self-regulation, and adaptive behaviour [12]. Early detection of psychological distress or mental illness is critical. The right treatment, care, and support can be life-changing for a mother and her infant.

Mindfulness is defined as the mental state of focusing one’s awareness on the present moment without judgement [13]. Practising mindfulness is known to have a wide range of benefits to mental wellbeing, including increased self-compassion, improved concentration, reduced rumination, and reduction in stress [14]. One intervention that appears promising in its benefits is the use of mindfulness meditation mobile applications (apps) [15]. These electronic interventions may be particularly helpful for self-managing mental health during health emergency situations, such as the recent COVID-19 pandemic, while maintaining quarantine and social distancing [16]. Online and mobile health technologies also have the potential to greatly improve access to care for patients in rural and remote areas, who experience documented disparities in maternity care and maternal health outcomes [17, 18].

Smith et al. [16] have previously examined a mindfulness intervention via a mobile app in an American prenatal population. In a randomised control trial, mothers (*n* = 80, 40 per group) who received the mindfulness app were encouraged to use it for 10 min per day for 30 days. Self-report questionnaires measuring stress (Cohen’s 10-item Perceived Stress Scale), anxiety and depression (Zigmond’s 14-item Hospital Anxiety and Depression Scale), and sleep disturbance (Patient-Reported Outcomes Measurement Information System (PROMIS) Sleep Disturbance Short Form) were administered at days 0, 14, and 30. A satisfaction questionnaire was also administered to ascertain feelings towards the mindfulness app. Participants who were in the intervention group reported lower levels of stress, anxiety and depression, and sleep disturbance following the use of the mindfulness app. Overall, satisfaction with the app was high.

While the effects of face-to-face mindfulness meditation have been studied in women in the perinatal period [15], and one study [16] has examined mindfulness via a mobile app in the prenatal population, no studies have examined the use of mindfulness app across the peripartum period. Further, no studies have explored the economic benefits of such an app. Despite this, women may be more receptive to changing their health behaviours and adopting mindfulness during pregnancy because of their concern for their unborn child [19]. The objective of this randomised controlled trial (RCT) is to assess the effect of a consumer-based mobile mindfulness app on perceived distress in maternity patients and provide an economic evaluation.

## Objectives {7}

The primary goal of the study is to assess the effectiveness of the Mater mindfulness app (a mobile app) to improve mental health outcomes in perinatal women. Secondary objectives are to evaluate the effectiveness of the app to improve mother-baby bonding, and mindful attention in users, to determine participant adherence, and to examine the economic benefits to the healthcare system of providing mindfulness support via a mobile app. The final objective will be to evaluate women’s satisfaction with the app.

## Trial design {8}

This study will be conducted in accordance with SPIRIT guidelines for clinical trial protocols. The study will be a stratified randomised controlled, superiority trial with two parallel groups and a repeated measures design. Women will be randomised into the intervention group (with full access to the Mater mindfulness app) or a passive control group (usual care). All participants will be assessed at four timepoints over the course of approximately 11 months (at 16 weeks’ gestation, 28 weeks’ gestation, 3 months postpartum, and 6 months postpartum) to assess differences between intervention and control groups. The PROMIS Global-10 survey will be used to calculate quality-adjusted life year (QALY) scores used to assess cost-effectiveness.

## Methods: participants, interventions, and outcomes

### Study setting {9}

The trial will be a single-site study conducted at the largest maternity hospital in Australia. The site, located in Brisbane, Queensland, manages an average of 10,000 births annually. This hospital provides a large range of antenatal care to women, including standard care by midwives to low-risk women, and specialty clinical care to high-risk women. A wide range of maternity models of care are available at the hospital, including specialty services for women who may be affected by substance use disorders, women with special needs, and refugee clinics. Participants for this study will be recruited from women who are attending both the public and private maternity clinics at this hospital.

### Eligibility criteria {10}

All pregnant women at less than 16 weeks’ gestation, attending the public or private maternity clinics at Mater Misericordiae in Brisbane, will be invited to participate in the study. Women must be 18 years or older and be proficient in English, as that is the only language the first iteration of the app will be created in. Women must also own a smartphone device that is capable of downloading and running the Mater mindfulness app.

### Who will take informed consent? {26a}

Eligible women will be sent a copy of the research information sheet and consent form via an SMS message. This will include a tick box where women may select to either participate or opt out of the study, and answer a question relating to the midwifery model of care, to allow for stratified randomisation. Failure to respond to the initial message will trigger a follow-up phone call by a research team member who will explain the study and request that the women select an option via the SMS-delivered consent form.

### Additional consent provisions for collection and use of participant data and biological specimens {26b}

Additional demographic and medical history data will be extracted from medical records. No sensitive or identifying data will be collected or stored on the App. De-identified survey data is collected via a university-run software program and stored on the hospital computer network.

## Interventions

### Explanation for the choice of comparators {6b}

The study compares the outcomes of an intervention group to a passive control group that undertakes usual care. A wait-list control or stepped wedge design would be inappropriate for this study as the app is tailored to specific timeframes within the pregnancy. However, all women will be given access to the app once they have completed the study.

### Intervention description {11a}

The Mater mindfulness app is a perinatal mindfulness-based app, co-designed by women with lived experience of perinatal mental illness, and clinicians with expertise in mindfulness and perinatal mental health. Final relaxation scripts were reviewed by a consumer advisory group to ensure suitability. The content of the app will consist of 40 relaxation exercises, tailored to different stages in the pre- (second trimester) and postpartum period (6 months after birth). The relaxation exercises will also be available for women to listen to on the Mater Mothers’ website.

The relaxation exercises in the app include a range of audio recordings targeting mindfulness, mother-infant bonding, relaxation, and meditation. There are also some videos of relaxation exercises to support focus. For example, the app will guide women to complete deep breathing exercises with their baby. There are also relaxation exercises completed prior to bedtime, while eating, with a partner, when pregnant, and towards the unborn baby, as well as when completing walks with and without a baby in a pram. Mindfulness-based approaches are used in a number of exercises, such as breathing in and out as women trace their fingers. See the Additional file 2 and Additional file 3 for relaxation exercise descriptions and selected transcripts. Each of the relaxation exercises is on average 3 min in length and ranging between 2 and 10 min. Each day there is one relaxation exercise that is highlighted on the home screen. On the second page of the app, there is a library of the relaxation exercises available.

The app also contains information (e.g. website, phone number, description) of a range of local and national support services that are pertinent to perinatal mental health, parenting support, child development, mental health hotlines, and partner/father mental health. The app has a mood-tracking function so that after the completion of each relaxation exercise, women rate their well-being with emoticons. Women are also affirmed with a message of encouragement once a relaxation exercise has been completed. This is recorded and viewed in a graph to assess change in mood over time. The colour scheme of the app can also be personalised based on the preferences of the woman (e.g. pink and blue, gradient from grey to green, orange and green, and turquoise and blue). The app tiles contain icons, and there is a brief description of the relaxation exercise, including the length of time for the exercise. The app is freely available and can be downloaded from the Apple and Android App Store.

### Criteria for discontinuing or modifying allocated interventions {11b}

Participants will be free to withdraw from the study at any time. Women who appear in distress will be flagged by the research team, removed from the study, and offered additional support. To ensure the validity of results, all data collected from participants up to the point of withdrawal will be included in the analysis, which will be conducted according to the intention-to-treat principle.

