### Provisions for post-trial care {30}

The data collected in this study is not expected to cause significant distress or discomfort to participants. However, in the event that participants experience distress in the course of this study, the participant information sheet will provide participants with information about support services they can contact. This will include Beyond Blue, Lifeline, and the research team. In addition, participants who score highly on the EPDS scale, or noted on this scale that they have thought of self-harm, will be flagged by the research team, and further support will be offered.

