### Outcomes {12}

Postnatal depression will be the primary outcome of the study. This will be measured using the Edinburgh Postnatal Depression Scale (EPDS). The primary outcome will be EPDS measured at 6 months postpartum. Changes in postnatal depression over time will also be assessed and will be determined by conducting the EPDS at four timepoints: 16 weeks’ gestation, 28 weeks’ gestation, 3 months postpartum, and 6 months postpartum. Secondary outcomes measured at the same timepoints will include measures of mother-infant bonding (using the *Mother-to-Infant Bonding Scale*), quality of life, and cost-effectiveness (using the *PROMIS Global-10*). The primary timepoints for these assessments will be timepoint 1 (16 weeks’ gestation) and timepoint 4 (6 months postpartum). Mindful attention (using the *Mindful Attention Awareness Scale*) will be measured at times one and four. Participant satisfaction with the app (using a bespoke survey described below) will be measured at the third timepoint (3 months postpartum), and participant adherence (measured with click analytics to detect the frequency of app use) will be examined once participants have completed the study (see Fig. 1). The study will also use click analytics to determine the frequency of app use. Demographic data and medical health information will be extracted from medical records for the purposes of inferential statistical analyses. Changes from timepoint 1 will be assessed for all health-related, repeated surveys. Measures will be analysed in aggregate form.

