## Assignment of interventions: blinding

### Who will be blinded {17a}

Care providers will not be aware of the assignment status of participants. Trial participants will not be blinded to their group allocation status. A member of the research team, not involved with patient care, recruitment, or group allocation, will email the intervention group instructions for downloading the online app and will provide technical assistance to participants. The data analyst will be blinded to participant allocation.

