#### The Edinburgh Postnatal Depression Scale (EPDS)

The EPDS is a 10-item questionnaire designed to screen women for symptoms of depression in the postnatal period [25]. Women completing the EPDS are asked to rate the option that best describes how they have felt in the past 7 days in response to a number of statements (e.g. “I have blamed myself unnecessarily when things went wrong.”). Items are scored on a 4-point scale, with response scores ranging from 0 to 3. Item scores are summed to produce a total score. Scores ranging from 0 to 9 indicate low levels of distress, scores from 10 to 12 indicate the presence of distress, and scores above 13 suggest a high presence of depressive symptoms. A minimum 4-point change in scores across timepoints is necessary to be deemed clinically significant [26]. The EPDS has been validated for use in both a prenatal and postnatal population [25, 27]. Women who score one, two, or three on item 10 (“The thought of harming myself has occurred to me”) will be addressed with further enquiry and support if necessary [28].

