## Statistical methods

### Statistical methods for primary and secondary outcomes {20a}

The primary analyses will be conducted according to the intention-to-treat principle. This means that participant data will be analysed based on the initial treatment assignment and not the treatment ultimately received. Descriptive statistics (mean/standard deviation, median/range, proportion/percentage) will be used to describe participants’ characteristics. Normality testing by visual assessment of the data will precede inferential statistical tests of continuous outcomes, such as questionnaire scores. The primary analysis of EPDS scores at 6 months postpartum will be conducted using a linear regression model to compare the intervention and control groups. This will be analysed using an independent samples *t*-test and further sensitivity analyses using analysis of covariance (ANCOVA) to determine the impact of the intervention on EPDS scores while controlling for covariates such as age and parity.

The mean change in EPDS from timepoint 1 to timepoint 4 will also be investigated. To estimate the changes within and between test groups at each timepoint, a linear mixed effects model for repeated measures will be used. The participant will be treated as a random effect, by means of the restricted maximum likelihood method (REML). The main effects of group, time, and a group-time interaction will be analysed. To determine the effect of the baby’s sex (which will only become known at timepoint two) on outcomes, the main effects of knowledge, sex, and a knowledge-sex interaction will also be measured. Additional potential covariates (age, parity, marital status, child disability, stillbirth or infant death, and previous episode of depression) will be included as fixed effects. Secondary outcomes of interest (mother-to-infant bonding, quality of life, and mindful awareness) will be analysed with the same strategy described above.

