### Methods in analysis to handle protocol non-adherence and any statistical methods to handle missing data {20c}

All data will be analysed using an intention-to-treat study design, regardless of protocol adherence. Missing responses within partially completed surveys will be handled as per the instructions in the scoring manual for each individual survey. Where timepoint data is missing, linear mixed model analysis will retain all data, and missing data will be assumed to be missing at random.

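### Women who seem distressed are taken out of the study, not just off the app, so those removed before 6 months lose their primary EPDS for a reason tied to that outcome

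*Protocol article*

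**What the plan says.** All references are to the protocol article.

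- **Criteria for discontinuing or modifying allocated interventions {11b}:** "Women who appear in distress will be flagged by the research team, removed from the study, and offered additional support". On the data, "all data collected from participants up to the point of withdrawal will be included in the analysis", under the intention-to-treat principle.
- **Outcomes {12}:** "The primary outcome will be EPDS measured at 6 months postpartum".
- **Statistical methods {20a}:** "The primary analysis of EPDS scores at 6 months postpartum will be conducted using a linear regression model". The section then names an independent-samples t-test, with ANCOVA as a sensitivity analysis. A mixed model for repeated measures is described separately, for change over time.
- **Missing data {20c}:** where a timepoint is missing, the mixed model keeps the remaining data and "missing data will be assumed to be missing at random".
- **Provisions for post-trial care {30}:** women with high EPDS scores or self-harm thoughts "will be flagged by the research team, and further support will be offered".
- **The EPDS section:** women who endorse the self-harm item "will be addressed with further enquiry and support if necessary". The same section describes scores of 10 to 12 as showing distress.

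Neither of the last two sections mentions removal.

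**The concern.** The heading of {11b} is about stopping or changing the intervention, but its text ends the woman's participation in the study. The trigger, distress, is close to what the primary outcome measures. Endpoint data are therefore lost by a decision of the research team, and selectively among the women whose 6-month scores are likely to be high.

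The analysis stays by assigned arm in name, but part of each randomised group has no endpoint for an outcome-related reason. The bias can run either way:

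- If the app works and flagging is even, more controls are removed and the observed difference shrinks.
- If one arm is flagged more readily, that arm looks better than it is. Participants are not blinded. The app arm also has an additional contact with the team: under {17a} a team member "will email the intervention group instructions for downloading the online app and will provide technical assistance to participants".

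It is also unclear which flagged women leave. {11b} joins flagging to removal, while {30} and the EPDS section join flagging to support only.

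**Working it through.** **1. The rule set against the analysis.** A woman removed after the 28-week or 3-month survey has no 6-month EPDS. The t-test or regression on that score uses no earlier EPDS values, so she drops out of it. A woman first flagged at 6 months keeps her score. The problem is confined to removals before the last timepoint.

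**2. The plan's own sample size.** With d = 0.50, two-sided 5%, 80% power and 1:1 allocation, the two-sample t-test needs 64 per arm, 128 in total. With 40% attrition, 128 / 0.6 = 213.3, rounded up to 214. Both stated figures reproduce. The allowance protects the number analysed, not against loss related to the outcome.

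**3. Simple normal model (assumptions, not in the article).** Work in SD units. Earlier distress D and 6-month EPDS Y have correlation ρ. The app lowers both by 0.50. Women with D > c are removed. With λ(x) = φ(x)/Φ(x):

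completer difference = 0.50 − ρ[λ(c) − λ(c + 0.50)]

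For 10% of controls removed, c = 1.2816, λ(c) = 0.1950 and λ(c + 0.50) = 0.0848, a gap of 0.1102. With ρ = 0.4 the result is 0.50 − 0.4 × 0.1102 = 0.456. With ρ = 0.7 it is 0.50 − 0.7 × 0.1102 = 0.423.

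| Controls removed | App arm removed | λ gap | Difference, ρ 0.7 to 0.4 | Power, 64 analysed per arm |
|---|---|---|---|---|
| 0% | 0% | 0 | 0.50 | 80% |
| 5% | 1.6% | 0.068 | 0.45–0.47 | 75–77% |
| 10% | 3.7% | 0.110 | 0.42–0.46 | 71–74% |
| 20% | 9.0% | 0.172 | 0.38–0.43 | 65–70% |

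Power uses the SD among the remaining women and holds 64 per arm fixed, so it reflects the selective loss and not any fall in numbers.

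**4. Simulation on the EPDS scale (assumptions).** Control mean 6.5, SD 5, skewed (gamma) scores capped at 30, correlation between visits 0.4 to 0.6, 400,000 women per arm. The app effect is either a shift of −1.0, −1.75 and −2.5 points (floored at 0) or a multiplier of 0.85, 0.75 and 0.65 at 28 weeks, 3 months and 6 months. Either way the true 6-month difference is about −2.3. A given share of women scoring 13 or more at 28 weeks or 3 months is removed at that visit.

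| Share of those women removed | Shrinkage, completers | Shrinkage, random-intercept model |
|---|---|---|
| 10% | 1–3% | 0–1% |
| 25% | 2–8% | between the 10% and 100% rows |
| 50% | 4–15% | between the 10% and 100% rows |
| 100% | 7–28% | 1–6% |

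In points, completers lose 0.02 to 0.63. At 10%, about 2.0% of controls and 1.0–1.5% of the app arm are removed, and 5–8% of controls who would score 13 or more at 6 months are lost. At 100%, 17–18% of controls and 9–14% of the app arm are removed, and 43–57% of those high-scoring controls are lost.

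If removal instead follows distress between 3 and 6 months that no survey records, at 100% the completer shrinkage is 6–22% and the mixed-model shrinkage 2–7%.

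**5. Uneven flagging with no true effect.** Flag 25% in one arm and 50% in the other. Completers show about 0.2 to 0.3 points in favour of the arm flagged more if the trigger is a recorded score, and 0.10 to 0.17 if it is not. The mixed model stays within about 0.02 and 0.04 points of zero.

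**The case against.** The strongest reply concerns size. The large figures remove every high scorer, yet {30} and the EPDS section describe only flagging and support for those women. Surveys are automated, and researchers with hospital roles have no direct contact with participants, so the team may rarely see distress other than through the EPDS. In that case removal follows recorded scores, and the mixed model recovers nearly all of the estimate. Section {20c} names that model for missing timepoints, and an analysis plan could give it the primary role. Uneven flagging is conjecture, since all participants are encouraged to tell the team about distress. Even 0.3 points is under a tenth of the 4-point change the article calls clinically significant. An article may also leave the definition of distress to the full protocol.

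Much of this stands. The 100% row is an upper bound, not a forecast. The uneven split is illustrative, and the extra contact in the app arm makes it possible, not likely. The lack of a defined trigger is not a fault in itself. It matters only because removal cannot be assumed to follow recorded scores, which is the condition under which the missing-at-random model works well.

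The central point is untouched. The article states removal from the study as a rule, provides for no later EPDS, and names a single-timepoint primary test. A mixed model can recover much of the estimate under its assumption, but no analysis recovers the uncollected scores that would show whether the assumption held.

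**Conclusion.** The concern holds. As written, the rule creates outcome-related missing data in the primary endpoint and works against the protocol's own intention-to-treat commitment.

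The frequency of removal, and so the size and direction of the bias, cannot be read from the article. Under the assumed inputs the loss is small if removal is rare (1–3% of the effect at 10% removal) and material if it is common (up to 28% among completers). The mixed model limits shrinkage to 7% or less in the scenarios run. The cut of 13, the removal shares, the EPDS mean, SD and correlations, and the effect patterns are all assumptions.

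It should be fixed: the defect is plain in the text, the lost scores cannot be obtained afterwards, and the correction is cheap.

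**What to change.** In {11b}, replace removal from the study with referral and support, plus discontinuation of the app where clinically needed. State that a flagged woman stays in her randomised group and continues to be sent the EPDS surveys to 6 months unless she withdraws consent for data collection. Use the same rule in {11b}, {30} and the EPDS section, say what triggers a flag, and report flags and app discontinuations by arm.

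The cost is an ethics amendment and continued review of flagged women's responses, including the self-harm item, which {30} and the EPDS section already require for participants. Surveys already go out by SMS, so there are no added visits, and the sample size does not change. The earlier the amendment, the fewer endpoints are lost.
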